### 2.4. Heart Function, Structure, and Heart Rate Variability (HRV)

Resting echocardiography will be performed on a Vivid S6 device (GE Healthcare) in accordance with the guidelines. The echocardiographic data analyzed will include: left ventricular (LV) ejection fraction, LV volume, and LV mass, regional or global wall motion abnormalities, LV diastolic function markers (mitral inflow with E/A ratio, tissue Doppler with lateral e′, and ′ septal, mean E/and ′), volumes and surfaces of the left and right atrium, right ventricular (RV) function markers (TAPSE, S wave ′, pulmonary artery systolic pressure (PAPs) estimated from the peak velocity of tricuspid regurgitation (RT)) will also be evaluated based on international recommendations [37]. Electrocardiogram (ECG) measurements will be performed at rest and in an exercise test on a treadmill (Inbrasport, Ergo13 for windows version 3.1.0.95) (Bruce protocol). Resting ECG will be measured using ECG Mac 800 (GE Healthcare), while exercise ECG will be measured using Edan SE-1515 DX12 (Edan, Shenzhen, China) with aerobic protocol performed on a treadmill. During the resting ECG, heart rate (HR), arrhythmias, conduction disturbances, and ventricular repolarization anomalies will be evaluated. During the exercise ECG, the maximum HR reached (absolute and as a percentage of the theoretical maximum HR for the age), rest/peak blood pressure, supraventricular and/or ventricular arrhythmias and/or T wave/ST segment anomalies and/or driving disorders will be recorded.

Heart rate will be recorded beat-to-beat using a cardio-frequency meter (Polar RS800CX, Polar Electro, Kempele, Finland) at a 1 kHz sampling rate to assess cardiac autonomic modulation. Using the chest strap and monitor, the individuals will be placed in a sitting position and remain at rest with spontaneous breathing for 25 min. The temperature of the room will be maintained at 20–23 °C and data will be collected in the morning, after a 4 h minimum fasting period. Participants will be asked to avoid consuming coffee, chocolate, or alcohol and take medications the night before the procedure. Heart rate variability will be performed on 256 consecutive RR intervals from the most stable segment of the tachogram. Only series with less than 5% error will be considered suitable for analysis. The data will be processed using the Polar Precision Performance software (Polar Electro, Finland) in moderate mode, followed by visual inspection. HRV will be assessed using linear methods (time and frequency domains and Poincaré Plot quantitative and qualitative analysis) using the Kubios^®^ HRV software (version 2.2, Kuopio, Finland).

### 2.5. Physical Functioning

Functional exercise capacity will be assessed using the 6-min walk test (6MWT), according to the guidelines of the European Respiratory Society/American Thoracic Society [38].

Handgrip strength will be estimated using an electronic dynamometer (Camry Electronic Handgrip Dynamometer, Model EH 101, Taiwan). Each test will be performed three times with a one-minute interval between the tests. The highest value obtained will be recorded for analysis. Peak force values will be measured.

### 2.6. Pulmonary Function and Respiratory Muscle Strength

Spirometry will be performed using a digital spirometer (MIR-Spirobank version 3.6) according to the guidelines for pulmonary function tests [39]. The results will be interpreted based on the recommendations of the American Thoracic Society and the European Respiratory Society [40] and the results compared with normative data from a Brazilian population [41]. The spirometric criteria for airflow limitation will be a fixed postbronchodilator ratio of FEV1/FVC < 0.70.

Respiratory muscle strength will be assessed using a manovacuometer (MVD 300, Globalmed, Porto Alegre, Brazil). The participant will be asked to sit in an upright position, with the chest and feet supported. Using a nose clip, the participant will be instructed to hold the manometer and press the mouthpiece firmly against the lips, avoiding air leakage. They will be asked to make a maximum inspiration of the residual volume to measure MIP and a maximal expiration of total lung capacity to determine MEP. In each evaluation, three measurements of MIP and MEP will be performed, with rest intervals of 30–60 s between measurements. The highest value will be recorded.

### 2.7. Mental Health

Mental health will be assessed employing questionnaires of cognitive function and anxiety and depression. The quality of sleep will also be evaluated. The Digit Span (numbers) questionnaire assesses the ability to focus and maintain attention, and the mental manipulation of information has two stages. Both conditions require participants to verbally repeat requested sequences in direct or reverse order. Both forward and reverse order has a total score of 14 points.

The Brazilian version of the beck depression inventory (BDI), containing 21 items, will be used to evaluate the intensity of depression symptoms, with responses rated on a Likert scale [42]. Scores range from 0 to 63 points (0–11 minimal; 12–19 mild; 20–35 moderate; and 36–63 severe). The Brazilian version of the Beck Anxiety Inventory (BAI), consisting of 21 statements, will be used to assess anxiety levels [42], with responses rated from 0 to 63 points (0–10: minimal anxiety; 11–19: mild anxiety; 20–30: moderate anxiety; and 31–63: severe anxiety). The HADS aims to measure symptoms of anxiety and depression and consists of 14 items, seven items for the anxiety subscale (HADS Anxiety) and seven for the depression subscale (HADS Depression). Each item is scored on a response scale with four alternatives ranging between 0 and 3. After adjusting for six items that are reversed scored, all responses are summed to obtain the two subscales. Recommended cut-off scores are <7 for improbable cases, 8–11 for doubtful cases, and ≥12 for probable cases [43].

The Epworth Sleepiness Scale (ESS), which assesses the nature and occurrence of daytime sleepiness, will be used to measure sleep quality [44]. It is self-administered and measures the possibility of napping in eight everyday situations. To grade the possibility of napping, the individual uses a scale from 0 to 3, where 0 is none and 3 is the highest probability of napping. Using a total score >10 as the cutoff point, it is possible to identify individuals with a high probability of EDS. Scores greater than 16 are indicative of severe sleepiness. The Pittsburgh Sleep Quality Index (PSIQ) questionnaire assesses sleep quality over the previous month [45]. It consists of 19 self-administered questions grouped into 7 components (subjective sleep quality, sleep latency, sleep duration, habitual sleep efficiency, sleep disorders, use of sleep medications, and daytime dysfunction) with weights distributed on a scale of 0 to 3. The scores of these components are then combined to produce an overall score ranging from 0 to 21, where the higher the score, the worse the sleep quality. An overall PSIQ score >5 indicates that the individual has great difficulties in at least 2 components or moderate difficulties in more than 3 components [46].

### 2.8. Data Capture and Management

Data from interviews, scales, and tests will be captured and stored in real-time using web-based google forms developed by our research team. The tabulation of results from manual tests will be performed by experienced research staff directly in the goggle drive database shared with the responsible research team. A team of experts will manage the database and they will provide access to the different research groups involved to enable them to conduct interim and final statistical analyses.

### 2.9. Summarization of Clinical Information and Feedback to Participants

The data gathered from follow-up assessments of participants previously infected with COVID-19 will be summarized in short health reports to be used for the benefit of long-COVID sufferers in need of clinical care. Potentially relevant clinical information will be fed back directly to the participant or included in a written report to be forwarded to the health provider who will continue to care for the individual.

### 2.10. Sample Size Estimation and Planning for Data Analysis

A Cohort of participants previously infected with SARS-CoV-2 and age-matched healthy participants will be randomly selected from the target population. Sample size calculation (G*Power, version 3.0; power = 0.80; α level = 0.05; medium-size effect) provided an estimated 75 participants. Therefore, 100 male and female participants aged 20–40 years will be recruited (over-recruitment compensates for dropouts during follow-up).

Participants will be stratified based on habitual physical activity levels (assessed by accelerometry-low versus normal physical activity levels), body composition (normal weight versus overweight or obese), and SARS-CoV-2 status (positive versus negative). In addition, a sub-analysis will be stratified based on sex (men vs. women).

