### 2.1. Study Design and Setting

A study design summary displaying the steps and evaluations of potential participants over approximately 18 months of follow-up is provided in Figure 1.

A follow-up period of approximately 18 months will be implemented. The procedures will be conducted for all participants at baseline, 6 weeks after vaccination, and 12 months after vaccination. After approval by the local Research Ethics Committee, patients previously infected with COVID-19 will be contacted to participate in the study through the local media and via electronic access to the participants’ database of Municipal Health Secretariat (MHS) of Presidente Prudente—São Paulo. Male and female patients aged 20–40 years with mild or moderate clinical COVID-19 infection will be recruited (intensive care cases will be excluded). An age-matched healthy control group that is negative for SARS-CoV-2 will also be enrolled. To detect previous SARS-CoV-2 infection, a lateral flow test for IgM and IgG antibodies will be conducted using internal anti-SARS-CoV-2 IgG and IgM ELISA kits. Participant exclusion criteria will include (1) presence of chronic non-communicable diseases, (2) smokers, (3) history of drug use, (4) medications such as anti-inflammatory drugs or antibiotics, (5) and frequent alcohol consumption (more than three times a week.

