### 2.3. Blood Collection and Analysis

At each time-moment, participants will visit the laboratory after overnight fasting. Forty milliliters of blood from an antecubital vein will be collected in a tube containing EDTA. To detect previous SARS-CoV-2 infection, a lateral flow test for IgM and IgG antibodies will be performed using internal anti-SARSr-CoV IgG and IgM ELISA kits. All patients (infected and non-infected with SARS-CoV-2) will be evaluated before (without vaccine) and after (with vaccine) the vaccination program. We plan to follow up the calendar vaccination of the São Paulo Government and recruit patients according to this schedule. Please, access information about the São Paulo State vaccination calendar in the link (https://www.prefeitura.sp.gov.br/cidade/secretarias/saude/vigilancia_em_saude/doencas_e_agravos/coronavirus/index.php?) (accessed on 5 January 2021). Phenotypes of immune cells will be characterized using multicolor flow cytometry, and monocytes, T cells, and Natural Killer (NK) cell subsets in whole blood will be quantified and characterized. T lymphocytes will be identified based on their positivity for CD3 and typical light scatter. Among positive CD3 cells, CD4^+^ T and CD8^+^ T cell subsets will be quantified. Based on the expression of CD14 and CD16, the classical (CD14++CD16−), intermediate (CD14++CD16+), and non-classical (CD14^+^CD16^++^) monocytes will be quantified. The NK cells will be defined as CD3^−^CD56^+^, and the two major subsets of NK cells, CD56^hi^CD16^−^ (CD56^bright^) and CD56^lo^CD16^+^ (CD56^dim^), will be identified. Biochemistry assays, including measurements of non-ester fatty acid (NEFA), glucose, triacylglycerol, total cholesterol, and HDL-c will be analyzed using a colorimetric method. Cortisol, insulin, and apolipoprotein A1 concentrations will be analyzed using ELISA. To determine the inflammatory status of the participants, the plasma concentrations of IL-1β, IFN-α, IFNγ, TNF-α, MCP-1, MIP-1β, IL-8, IL-10, IL-12p70, IL-17A, IL-18, IL-23, IL-33, IL-1ra, IL-2, IL-6 will be measured using the LUMINEX method.

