## 3. Discussion

This protocol describes an ambitious follow-up study that will be conducted in adults previously infected with COVID-19 (before and after vaccination program), highlighting long-term consequences of COVID-19 and its correlation with physical activity, body composition, and cross-linked with vaccination in the Brazilian population. Our hypothesis links reduced visceral adipose tissue deposits (which exhibit an anti-inflammatory profile, as hypoleptinemia and hyperadiponectinemia) with higher physical activity levels as central factors in reducing the severity of SARS-CoV-2 aggression, promoting metabolic programming of immune cells (favoring anti-inflammatory response), protecting the cardiovascular system, and general clinical profile.

Patients with COVID-19 who were consistently inactive and malnutrition had a greater risk of hospitalization, admission to the ICU, and death due to COVID-19 compared with patients who were consistently meeting the minimum physical activity guidelines (150 min/week) [27,47,48]. Longitudinal cohort studies of individuals who developed severe COVID-19 are being conducted to investigate possible symptoms and long-term clinical and functional alterations [49,50]. Longitudinal follow-up studies reporting persistent symptoms and sequelae of COVID-19 in mild and moderate patients are also needed in order to understand the intrinsic physiological mechanisms involved in these processes, their potential protective factors, and public health policies needed for treatment in the post-pandemic period in order to substantially minimize long-term chronic sequelae.

In addition to investigating an overlooked population, one advantage of the study proposed here is that we will conduct comprehensive symptom and clinical assessments of long-COVID manifestations pre- and post-vaccination. Potential limitations include the fact that we will rule out the presence of current re-infection based only on the absence of clinical signs and symptoms, rather than on the basis of a negative RT-PCR test. We will also only assess a specific, young population.

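### The sample is described as randomly selected from the target population, but infected patients are recruited partly through local media, so it is at least partly a volunteer sample and this is not listed as a limitation

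*Protocol article*

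**What the plan says.** Three sections of the protocol article bear on how people enter the study.

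- **Section 2.10** (sample size and planning for data analysis) makes a claim about sampling: "A Cohort of participants previously infected with SARS-CoV-2 and age-matched healthy participants will be randomly selected from the target population". It covers both the infected cohort and the healthy comparison group.
- **Section 2.1** (design and setting) gives the practical route for the infected group: "patients previously infected with COVID-19 will be contacted to participate in the study through the local media and via electronic access" to the database of the municipal health secretariat.
- **Section 2.3** (blood collection) sets the pace of recruitment: "We plan to follow up the calendar vaccination of the São Paulo Government and recruit patients according to this schedule".

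The Discussion names two limitations. Current re-infection is ruled out on clinical grounds without RT-PCR, and "We will also only assess a specific, young population". The separate Limitations section deals only with re-infection during follow-up. Neither mentions how participants were selected.

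**The concern.** In a random sample, each member of a defined population has a known chance of being chosen, and the investigator makes the choice. Someone who answers a media notice makes that choice personally, with an unknown probability. The two descriptions cannot both be true of the media recruits.

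This matters for two reasons.

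1. **Population inference.** The Discussion speaks of long-term consequences in the Brazilian population and of public health policy. A statement that the sample was drawn at random lends such inference a support that the recruitment described does not provide.
2. **The main objective.** The Background asks whether physical activity and adipose tissue determine systemic inflammation and clinical function. Willingness to volunteer could depend on activity or interest in fitness (the exposure side) and on persistent symptoms (the outcome side). If it depends on both, selection can distort the association itself as well as the description of the sample. Readers who take the random-selection statement at face value would not look for this.

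**Working it through.** No arithmetic decides this point. It rests on setting the claim against each recruitment step described.

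**Step 1: what the claim requires.** Section 2.10 needs a defined frame and a random draw from it.

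**Step 2: the database route (Section 2.1).** The municipal database lists previously infected people and could serve as a frame. Contacting people through it is compatible with a random draw of whom to contact. No draw is stated, but none is ruled out.

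**Step 3: the media route (Section 2.1).** The plan says that infected patients "will be contacted to participate in the study through the local media and via electronic access to the" database, so media is a route in its own right. Media responders are not drawn from a list. A random draw from the database, even if done, would not cover them. This step contradicts the claim.

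**Step 4: the calendar (Section 2.3).** Recruitment follows the public vaccination schedule. That restricts when people can be enrolled and describes no draw. It does not prevent one, because a draw could be made within each calendar window.

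**Step 5: the limitations.** The Discussion and the Limitations section cover re-infection and the young age range. Self-selection does not appear, so nothing elsewhere corrects the claim.

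**Can the effect be sized?** Let p be the proportion of eligible patients with a given trait, and R the response probability of those with the trait divided by that of those without it. The proportion with the trait among volunteers is then

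pR / (pR + 1 − p).

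At R = 1 this returns p and there is no distortion. Above 1 the trait is over-represented, and below 1 it is under-represented. The article gives neither p nor R for symptoms, activity or anything else, nor the share of participants expected from media. Any number put in would be an assumption, and even the sign of the distortion is open.

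**Effect on stated figures.** None. The estimate of 75 participants and the target of 100 do not depend on how people are sampled.

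**The case against.** The strongest reply has four parts.

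1. **The conflict is partial.** The database route fits a random draw, and a condensed article may leave the mechanics of that draw to the full protocol. This stands for the database route. It does not help the media route, which the article itself names.
2. **The study compares groups and plans no prevalence estimate.** The planned strata are activity, body composition and SARS-CoV-2 status, so representativeness may seem beside the point. This stands against using an inflated symptom prevalence as evidence of harm. It does not remove the concern for the comparisons, which selection on both exposure and outcome can also bias.
3. **The direction is unknown.** A reader might infer that people with lasting symptoms are over-represented, and Section 2.9 offers a possible incentive: "short health reports to be used for the benefit of long-COVID sufferers in need of clinical care". The article does not support that as fact. It gives no response data. The exclusions for chronic disease and for certain medicines, together with the demanding exercise tests, could keep symptomatic people away. Volunteers keen on fitness could also shift the sample. This objection stands in full.
4. **The control group is a separate matter.** A reader might also object that no frame is given for the controls ("An age-matched healthy control group that is negative for SARS-CoV-2 will also be enrolled") and that they are matched on age alone. The source of controls is a detail that an article commonly leaves to the full protocol. Matching on age without sex is a design choice, and Section 2.10 plans a sub-analysis by sex. Neither is an error, and neither is part of this point.

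**Conclusion.** The point holds in a limited form. Section 2.10 claims a property, random selection from the target population, that the media recruitment in Section 2.1 contradicts and that no described procedure supplies. The sample is at least partly a volunteer sample. Selection by symptoms, activity or interest in health is possible, with unknown direction and unknown size, and the limitations omit it.

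The conclusion assumes only that media responders decide for themselves whether to come forward. It needs no assumed prevalence or response ratio, and it does not say that any result will be biased in a particular direction. The study remains feasible as designed. What changes is how far its findings can be generalised, and how carefully the associations with activity and body fat must be read.

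**What to change.** Choose one of two routes.

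- **Keep the claim for the part of the sample where it can be true.** Draw the people to contact at random from the municipal database, within each window of the vaccination calendar that Section 2.3 follows. Treat media recruits as a second source, recorded as such, and do not call them randomly selected.
- **Withdraw the claim.** Delete the random-selection wording from Section 2.10 and describe a volunteer sample.

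In either case:

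1. record the recruitment source for each participant;
2. report the numbers contacted, responding and enrolled by route (for media, those who made contact, since the number reached cannot be known);
3. repeat the main analyses without media volunteers, as a sensitivity analysis;
4. add selection bias, of unknown direction, to the limitations.

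**Cost.** One extra field in the database, a little more analysis, and a less favourable description of the sample. The sensitivity analysis loses precision. If a share m of a group came through media, the standard error of that group's mean grows by a factor of about 1/√(1 − m), other things equal. The article does not give m, and with small strata the loss could be appreciable. That analysis should therefore be read as a check on direction and stability, without expecting it to reach significance by itself.
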